## Abstract

**Background:**

Living donor kidney transplantation (LDKT) is the most successful form of renal replacement therapy in terms of wait time and survival rates. However, we observed a significant inequality in the number of LDKT performed between the Dutch and the non-Dutch patients. The objective of this study is to adapt, implement and test an educational home-based intervention to contribute to the reduction of this inequality. Our aim is to establish this through guided communication together with the social network of the patients in an attempt that well-informed decisions regarding renal replacement therapy can be made: *Multisystemic Engagement & Nephrology*. This manuscript is a detailed description of the Kidney Team At Home-study protocol.

**Methods and design:**

All patients (>18 yrs) that are referred to the pre-transplantation outpatient clinic are eligible to participate in the study. Patients will be randomly assigned to either an experimental or a control group. The control group will continue to receive standard care. The experimental group will receive standard care plus a home-based educational intervention. The intervention consists of two sessions at the patient’s home, an initial session with the patient and a second session for which individuals from their social network are invited to take part. Based on the literature and behavioural change theories we hypothesize that reducing hurdles in knowledge, risk perception, subjective norm, self-efficacy, and communication contribute to well-informed decision making and reducing inequality in accessing LDKT programs. A change in these factors is consequently our primary outcome-measure. Based on power calculations, we aim to include 160 patients over a period of two years.

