### Objectives

The objective of the Kidney Team At Home-study is to contribute to the reduction of ethnic inequalities in LDKT health care access. We translated this objective in two concrete research questions. The primary research question is to investigate whether this home-based educational intervention results in improved knowledge and communication as compared to the standard educational care. The intervention should in this matter help the patients and their social network to reach a *well-informed decision* with regard to the most suitable treatment option. This is deliberately set as a primary research question, as a well-informed decision does not necessarily have to lead to LDKT. The secondary research question is to investigate whether this intervention leads to reduced ethnic inequality in the pursuit of LDKT. This is operationalized by looking into distribution of LDKT activities between the experimental and control group. This study protocol provides a detailed description of the Kidney Team At Home-study and the design of the randomized controlled trial (RCT) in line with the CONSORT (consolidated standards of reporting trails) checklist [27,28].

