#### Experimental condition

The intervention consists of two sessions at the patient’s home. Session One: Firstly, at the beginning of the session the patient completes the baseline measurement. Secondly, the family network of the patients will be depicted on a genogram the educator in order to get familiar with the family structure and to recognize the values of that social system. The observation of the educators during the sessions represents an important source of information about how the present individuals relate to each other. In fact, the educators never rely solely on the individual’s verbal self-description to investigate social relations. Only by observing how the individuals behave with each other can the educators support or reject hypotheses based on self-reports. During this first session the educators watch for non-verbal clues that confirm or contradict what the social system is telling them. As the educators form tentative hypotheses about psychosocial hurdles, they do not offer advice or share their observations to avoid defensiveness. They rather focus on engagement by showing helpful interest while listening to the needs of the individuals and reinforcing the strengths of the respective social system. At the end of the first session the educators will make an inventory of individuals that the patient will invite for the second session. The educators may help in inviting identified individuals. The invitation will be conducted verbally accompanied by a brochure containing the 1) study purpose, 2) education content, and 3) contact information of the educators.

Session Two: The educators organize this session in such a way that they will do ‘what ever it takes’, in line with one of the basic principles of MST, to make this event as patient-tailored as possible. This means that the intervention will usually take place in the evenings and weekends since most friends and family members are working during office hours. The primary goal of this intervention is educational, therefore, it is not necessary that all the invitees are potential donors. The baseline-outcome measurement for the invitees will take place at the start of the second session. In exceptional cases multiple sessions are required in order to reach the goals set for those sessions. Table
1 shows the topics that will be discussed during the second session.

**Table 1 T1:** The educational topics discussed in the second session

		

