#### Primary outcome measures

##### Knowledge

Because there was no suitable instrument to measure knowledge on kidney diseases and all the possible RRT’s, we developed the Rotterdam Renal Knowledge-Test (RRK-T) based on Devin et al (1990), Stothers et al (2005) and Rodrigue et al (2007). The RRK-T consists on 30 true / false or multiple choice questions on kidney disease, dialysis and transplantation with a living or deceased donor [29]. For example, *‘Renal replacement therapy is necessary when the kidneys function for only 50%’.* A clinically significant change will be indicated by 8 points of difference compared to the baseline measurement and is additional to passing the clinical cut-off point of 17 points (each correctly answered questionnaire is awarded 1 point) [30].

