##### Intention

This factor measures the extent to which patients and invitees plan to / are willing to discuss RRT’s or if they would give or accept a kidney [25,26]. For example: *‘How much do you want to donate a kidney to the patient’ (1 = not at all - 5 = very much).*

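### The primary outcome is two, five or seven variables depending on the section, and nothing says which or how many must change for a positive answer

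*Protocol article*

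**What the plan says.** The sets are given in three places in the Protocol article.

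- **Objectives (two variables).** The primary research question is "whether this home-based educational intervention results in improved knowledge and communication as compared to the standard educational care".
- **Abstract, Methods and design (five variables).** The hypothesis is that "reducing hurdles in knowledge, risk perception, subjective norm, self-efficacy, and communication contribute to well-informed decision making", followed by "A change in these factors is consequently our primary outcome-measure".
- **The section headed "Primary outcome measures" (seven variables).** Its subheadings are knowledge, attitude, risk perception, communication, self-efficacy, subjective norm and intention.

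The Discussion restates the primary question more generally, as lowering hurdles to living donor transplantation (LDKT). The Conclusion ties support for the hypotheses to the same general idea.

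Statistical analysis assigns mixed models to the primary outcome variables, in the plural. It refers elsewhere to a primary outcome in the singular, and to key efficacy variables that are not defined. It gives no test level, order of testing or success rule for them. The 0.05 appears under Sample size calculation, for a two-sided comparison of LDKT proportions, which is a secondary outcome.

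Five of the seven scales (attitude, communication, self-efficacy, subjective norm, intention) are described for both patients and invitees. For invitees, "The baseline-outcome measurement for the invitees will take place at the start of the second session"; they receive the post-measurement at the end of that session and may mail it back within a week. The Control condition section describes no invitees.

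**The concern.** The primary outcome set decides what the trial may claim. With three sets in print, a result on attitude alone would be a primary finding under one section, and no primary finding at all under the other two. A mixed result could be presented under whichever list suits it.

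The scales are also not interchangeable. The Sample size calculation section itself expects a large effect on knowledge and says self-efficacy would need a larger sample. A choice of list made after the data are seen could therefore favour the easier outcomes.

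The open list also reaches the analysis population. That population requires post-baseline data on one or more of the undefined key efficacy variables, so who is analysed may depend on which list is meant.

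For invitees the problem is one of comparison. As the text describes it, they enter through Session Two in the experimental arm only, so a change in their scores has no randomised counterpart.

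**Working it through.** **Setting the lists side by side**

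| Variable | Objectives | Abstract | Primary outcome section |
|---|---|---|---|
| Knowledge | yes | yes | yes |
| Communication | yes | yes | yes |
| Risk perception | no | yes | yes |
| Subjective norm | no | yes | yes |
| Self-efficacy | no | yes | yes |
| Attitude | no | no | yes |
| Intention | no | no | yes |
| **Total** | **2** | **5** | **7** |

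**The plan's own figure.** The article states no overall error rate for the primary outcomes, so there is none to reproduce. Its one design figure, 78 per group, concerns the LDKT proportion. It cannot be reproduced because the two proportions are not given. Many pairs fit, for example 0.20 against 0.405 without continuity correction, or 0.20 against 0.419 with it. It does not bear on which list is primary.

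**Chance of at least one false positive.** Assumptions, none of them stated in the article: every null hypothesis is true, each outcome is tested two-sided at 0.05, and any one significant result counts as success. For k independent tests the chance is 1 − 0.95^k.

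- k = 2: 1 − 0.9025 = 9.75%
- k = 5: 1 − 0.7738 = 22.6%
- k = 7: 1 − 0.6983 = 30.2%

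For two-sided normal tests these values are also the upper limit under any correlation (Šidák's inequality). The scales are probably correlated. With an assumed common correlation, simulating equicorrelated normal statistics (400,000 draws) gives:

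| Outcomes | correlation 0.3 | 0.5 | 0.7 |
|---|---|---|---|
| 2 | 9.6% | 9.0% | 8.4% |
| 5 | 20.9% | 18.3% | 14.8% |
| 7 | 27.3% | 22.9% | 17.8% |

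**After an adjustment.** At 0.05/k each, independent tests give 1 − (1 − 0.05/k)^k = 4.9% for k = 2, 5 or 7.

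**Price in detectable difference.** The target of 160 patients gives 80 per arm if allocation is equal and data are complete (assumed). For 80% power the normal approximation is d = (z for 1 − α/2 + 0.842) × √(2/80), with √(2/80) = 0.158.

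- α = 0.05: (1.960 + 0.842) × 0.158 = 0.44 SD; 0.446 by the t-test
- α = 0.025 (two outcomes): (2.241 + 0.842) × 0.158 = 0.49 SD; 0.491 by the t-test
- α = 0.05/7 (seven outcomes): 0.56 SD; 0.565 by the t-test

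**Invitees.** Both measurements bracket Session Two: baseline at its start, post-measure at its end or within a week. The Control condition section mentions neither invitees nor a measurement of them. The text therefore supports a before-after description in one arm only.

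**The case against.** The three places do not have equal standing. The Objectives pose a question in prose and the Abstract is a summary; only the primary outcome section is operational. Its seven headings match the constructs that the Background takes from its behavioural model, with subjective norm in place of social influence. A reader could reasonably take the seven as the real list. That is fair, but the Abstract expressly calls a change in its five factors the primary outcome, and the Objectives limit the primary question to two. These are positive statements that disagree, so neither condensation for a journal nor an analysis plan that is not shown explains them.

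A reader might infer that the trial tests every outcome at an unadjusted 0.05 and so carries a 30% false-positive risk. The document does not support that. Its 0.05 belongs to the sample-size calculation, no any-one rule is stated, and a multiplicity rule may sit in a document not shown.

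A reader might also infer that attitude and intention contradict the rationale that "a well-informed decision does not necessarily have to lead to LDKT". Intention does ask patients and invitees "if they would give or accept a kidney", but both scales also cover discussing renal replacement therapy, and LDKT itself is a secondary outcome. That is a tension, not a contradiction.

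On invitees, the analysis population consists of randomised patients, no explicit effectiveness claim is made for invitees, and the design figure is not shown. The point therefore rests on the text alone and guards against a claim that might later be made.

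**Conclusion.** The concern holds in this form: the article defines the primary outcome as two, five and seven variables, and does not say which or how many must change for the primary question to be answered positively. That contradiction can be seen in the text and needs no assumption.

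The size is conditional. With each outcome at two-sided 0.05 and any one sufficing, the false-positive chance is at most about 10%, 23% or 30% for two, five or seven outcomes, and about 18-27% for seven at assumed correlations of 0.7-0.3. These figures show what is at stake while list and rule stay open. They are not the trial's actual error rate, which cannot be derived from what the article states.

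The invitee point holds on the text as described, with less certainty because the design figure is missing.

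**What to change.** Use one primary list in the Abstract, Objectives, primary outcome section, Statistical analysis and Discussion. State with it a success rule that holds the overall two-sided error at 0.05, fixed before results are seen.

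The option closest to the stated research question is patient knowledge (the RRK-T) and patient communication, tested with Holm: the smaller p-value against 0.025 and, if that passes, the other against 0.05. The remaining five scales become secondary or explanatory. Keeping a longer list with an explicit alpha allocation, or naming a single primary outcome, would also resolve the matter. Define the key efficacy variables by reference to the chosen list.

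Report invitee scales as within-group change, from the start of Session Two to its end or up to a week later, without a randomised effectiveness claim.

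The cost is more than wording: the text must be reconciled and the listed primary set of a registered, ethics-approved trial amended. For two outcomes the detectable difference rises from about 0.45 to 0.49 SD. That figure comes from a simple t-test with 80 complete patients per arm; the planned mixed model in a modified intention-to-treat set may differ somewhat.

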**Discussion:**

If we are able to show that this home-based group educational intervention contributes to 1) achieving well-informed decision regarding treatment and 2) reducing the inequality in LDKT, the quality of life of patients will be improved while healthcare costs are reduced. As the intervention is investigated in a random heterogeneous patient group in daily practice, the transfer to clinical practice in other kidney transplant centers should be relatively easy.

**Trial registration:**

Netherlands Trial Register, NTR2730.

## Background

Patients with end-stage renal disease have various options for renal replacement therapy (RRT): hemodialysis, peritoneal dialysis, deceased donor kidney transplantation (DDKT) and living donor kidney transplantation (LDKT). Although dialysis is a life-saving treatment, the patient is faced with a substantial loss of quality of life and a significantly increased risk of morbidity and mortality [1]. At least one quarter of the patients die on the wait list for DDKT [2]. The calculation of the time spent on the wait list for a DDKT starts on the first day of dialysis and is on average three to five years in the Netherlands [3]. Research shows that LDKT is associated with significant patient and graft survival benefits when compared to DDKT [4]. One of the benefits of early LDKT is avoiding or minimising time on dialysis. However, one of the main concerns among patients is the health of the living donor. Studies have shown that among healthy screened individuals, the health risks for the donor are limited [5]. The donor is usually admitted for 3–4 days for the nephrectomy, can resume preoperative social and professional activities within four to six weeks and in general the perceived quality of life remains the same [5,6]. LDKT rates have steadily been increasing and now exceed those of DDKT in the Netherlands [3]. However, there appears to be an inequality in access to the LDKT program between Dutch and the non-Dutch patients. In our center 44% of patients on the wait list for DDKT are from non-Dutch descent [7]. However, non-Dutch patients represent only 18% of the patients transplanted via the LDKT program (period: 2000–2010). Therefore, fewer non-Dutch than Dutch benefit from the advantages of LDKT. This inequality is also present in other western countries [8-10]. This health care inequity needs to be addressed [11,12]. This discrepancy is partly attributable to medical, socio-economic and ethnic factors, which exert an independent significant influence on the chance of receiving a LDKT [7]. Due to an accumulation of unfavourable factors in the non-European population, their chances for a LDKT dropped to only 10% compared to the reference population (69%) [13]. Of the socio-economic hurdles, health insurance is less relevant in the Netherlands due to a health insurance system which is accessible for all Dutch citizens. Other possibly contributing factors to this inequality are potentially modifiable psychosocial (e.g. patient education, cognitions and emotions) and culture-specific factors (social influences, communication attitudes) [14,15]. The Kidney Team At Home-study focuses on addressing those potentially modifiable factors in a home-based educational intervention.

In response to this situation, we developed an educational program based on some of the principles of Multi System Therapy (MST) [16]. MST is an evidence-based therapy, which has been developed for derailed adolescents and families. Such serious pathology is unlikely to be found in the current study population. This means that the intervention applied here will be much less intense than MST in a pure form. The current intervention is an adaptation of the intervention developed by Rodrigue, which was also MST-based and proven to be effective in reducing inequality in patients with end-stage renal disease [17]. The intervention was adapted to the Dutch situation with regard to the culture specific factors and the content of the education appropriate to the Netherlands. We designed our intervention with respect to the MST framework in such a way that we strive for engagement of the patient’s family and social network in the disease process: *Multisystemic Engagement & Nephrology*.

We developed an intervention protocol based on empirical data on psychosocial hurdles to LDKT and influential theories from health psychology that focus on decision-making process and behavioural change. A close fit was found between data-driven hurdles and the following theory: Attitude-Social influence-Efficacy model (ASE-Model) [18]. The ASE-Model is based on the theory of Theory of Planned Behaviour (TPB) of Fishbein and Ajzen [19] and is supplemented by elements from the Social Cognitive Theory (SCT) of Bandura [20]. ASE has a wide scientific acceptance and represents a theoretical framework for explaining behaviour by connecting attitude, social influence, self-efficacy, knowledge, skills (communication), and barriers and resources (risk perception) to intention and behaviour. Firstly, the factor regarding ‘*attitude*’ in this theory is based on 1) the belief that people think that a certain behaviour will have positive or negative consequences and 2) their evaluation of the according consequences. In other words, attitude is a function of how we integrate the information that we have on a subject. Secondly, *social influence* is defined as the approval or disapproval of the pursued behaviour by others within the patient’s social network. Thirdly, *self-efficacy* looks at the extent to which individuals believe in their own abilities in relation to a particular behaviour. These factors influence a person’s *intention* to carry out certain behaviour. Empirical data in this area has shown that factors such as *knowledge, risk perception, attitude, communication, social influence, self-efficacy and intention* reveal good predictive values in the light of living organ donation [21-26].

### Objectives

The objective of the Kidney Team At Home-study is to contribute to the reduction of ethnic inequalities in LDKT health care access. We translated this objective in two concrete research questions. The primary research question is to investigate whether this home-based educational intervention results in improved knowledge and communication as compared to the standard educational care. The intervention should in this matter help the patients and their social network to reach a *well-informed decision* with regard to the most suitable treatment option. This is deliberately set as a primary research question, as a well-informed decision does not necessarily have to lead to LDKT. The secondary research question is to investigate whether this intervention leads to reduced ethnic inequality in the pursuit of LDKT. This is operationalized by looking into distribution of LDKT activities between the experimental and control group. This study protocol provides a detailed description of the Kidney Team At Home-study and the design of the randomized controlled trial (RCT) in line with the CONSORT (consolidated standards of reporting trails) checklist [27,28].

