### Design & procedure

In this prospective RCT all patients will be invited to participate by the educators after the consultation with the transplant nephrologists. During the face-to-face informational consultation the patient will receive written and verbal information on the aims and procedures of the study. Spouses, relatives or friends accompanying the patient to the hospital may be present during this consultation. Our target is to include 80 patients of Dutch origin and 80 patients of non-Dutch origin in the study over a period of two years in order to compare effectiveness of the intervention among these two groups. With respect to the inequality in LDKT, patients of non-Dutch origin will inherently be overrepresented in the study. After informed consent is obtained, patients will be randomized to either the control or the experimental group. The control group will receive standard care. The experimental group will receive standard care plus a home-based educational intervention. In the face of the equity principle, we will provide all the study materials (e.g. brochures, questionnaires) in the six most common foreign languages in the Rotterdam municipality namely, English, Arabic, Turkish, Papiamento, Portuguese and Modern Hindi [29].

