#### Secondary outcome measures

Secondary outcomes are operationalized in terms of behaviour that may lead to LDKT or LDKT itself. This is divided into three categories: the number of applications for LDKT evaluation, the number of actual evaluations for LDKT, and the number of LDKT’s. These outcomes will be monitored using the patient’s medical records during the year following the intervention date. Furthermore, we will also monitor the timeframe between the intervention and the moment that the event arises (time-to-event).

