Finally, semiparametric regression analysis will be employed using Cox Proportional Hazard Model to examine the significance of the contingency between the hazard for an event of the experimental and control group on the secondary outcome variables. This model enriches the analysis by incorporating covariates in the regression equation (e.g. age, gender, ethnicity, dialysis time). Time-to-event graphs will be depicted for the experimental and control group separately. Patients with a LDKT will be regarded as having the ‘event’ whereas patients who continue dialysis during the follow-up period will be censored. DDKT is modeled as a competing event and therefore patients who take-up this treatment will also be censored.

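### The secondary question asks whether ethnic inequality in LDKT falls, but its stated operationalisation compares only the two arms, and that comparison can be positive while the Dutch/non-Dutch gap is unchanged or wider

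*Protocol article*

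**What the plan says.** All references are to the protocol article.

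- **Objectives**, the question: "The secondary research question is to investigate whether this intervention leads to reduced ethnic inequality in the pursuit of LDKT".
- **Objectives**, next sentence, how it is to be answered: "This is operationalized by looking into distribution of LDKT activities between the experimental and control group".
- **Design & procedure**, recruitment: "Our target is to include 80 patients of Dutch origin and 80 patients of non-Dutch origin in the study", and the reason given is "in order to compare effectiveness of the intervention among these two groups".
- **Secondary outcome measures**: "the number of applications for LDKT evaluation, the number of actual evaluations for LDKT, and the number of LDKT’s", followed for one year after the intervention date, plus time to event. None is defined by ethnic group.
- **Sample size calculation**: at least 78 patients per study group, based on the LDKT proportions of the control and experimental groups in a previous trial.
- **Statistical analysis**: the Cox model examines "the hazard for an event of the experimental and control group on the secondary outcome variables". It is described as "incorporating covariates in the regression equation (e.g. age, gender, ethnicity, dialysis time"). For the display, "Time-to-event graphs will be depicted for the experimental and control group separately".
- **Discussion**: the secondary question is put as whether LDKT rates rise in diverse populations. That is not the same as a smaller gap.

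**The concern.** Inequality is a difference between Dutch and non-Dutch patients. A reduction in inequality is therefore a difference between arms in that difference, an arm-by-ethnicity contrast. The Objectives ask for this and in the next sentence replace it with a comparison of arms. Ethnicity as a main-effect covariate adjusts the arm effect; it does not estimate whether the gap has changed.

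The two questions can have different answers. If the intervention helps Dutch patients more than non-Dutch patients, the arm comparison is positive and the inequality has grown. An analyst following the stated operationalisation would report that result as a favourable answer to the inequality question. Reducing the inequality is one of the two benefits that the abstract hopes to show, so the wording affects what the trial can claim.

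**Working it through.** **1. The plan's own figure.** The 78 per group cannot be reproduced because the article does not give the two LDKT proportions. With two-sided alpha 0.05, power 0.80 and a continuity correction, it fits many pairs, for example 10% vs about 29%, 20% vs about 42%, 30% vs about 53%, or 40% vs about 64%. Exact Fisher power at 78 per group is 0.79 to 0.82 for these. In every case it is a sample size for the overall arm contrast.

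**2. Assumptions.** The article gives neither event rates by ethnic group nor the split within them. I assume the 80 Dutch and 80 non-Dutch patients divide evenly between arms, so 40 per cell. All rates below are illustrative.

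**3. Pooled effect against change in gap.** With equal cells:

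- pooled rate in an arm = (Dutch rate + non-Dutch rate) / 2
- gap in an arm = Dutch rate − non-Dutch rate
- change in gap = experimental gap − control gap

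Control to experimental rates:

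| Dutch | Non-Dutch | Pooled | Gap (points) | Pooled test significant |
|---|---|---|---|---|
| 30→52% | 10→20% | 20→36% | 20→32 | about 63% |
| 30→52% | 10→32% | 20→42% | 20→20 | about 87% |

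The last column is simulated, with 80 per arm and an uncorrected two-proportion test. Fisher's exact test gives 55% and 83%. The second row's pooled rates, 20% vs 42%, are one of the pairs that 78 per group fits.

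**4. Same pooled result, three different answers.** Each set below gives pooled rates of 27.5% vs 49.5% and about 82% power by the normal approximation:

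| Dutch | Non-Dutch | Gap (points) |
|---|---|---|
| 40→62% | 15→37% | 25→25 |
| 40→70% | 15→29% | 25→41 |
| 40→50% | 15→49% | 25→1 |

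The pooled contrast cannot tell these apart. The assumed rates set the size of the example, not the logic.

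**5. The scale matters.** Under proportional hazards and without censoring, HR = ln(1 − p_experimental) / ln(1 − p_control).

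- First row of step 3: Dutch ln(0.48)/ln(0.70) = 2.06; non-Dutch ln(0.80)/ln(0.90) = 2.12. The ratio of hazard ratios (non-Dutch to Dutch) is about 1.03, close to null, while the absolute gap widens by 12 points.
- Second row: Dutch 2.06; non-Dutch ln(0.68)/ln(0.90) = 3.66. The ratio is about 1.78, in favour of non-Dutch patients, while the absolute gap does not move.

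A Cox interaction and a difference in absolute gaps are therefore two estimands and can disagree.

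**6. Precision of the absolute contrast.** SE = √[Σ p(1 − p)/40] over the four cells. For the first row of step 3: √[(0.21 + 0.2496 + 0.09 + 0.16)/40] = √0.01774 = 0.133, so the 95% interval is about ±1.96 × 13.3 = ±26 points. At average rates of 20% to 50%, the smallest change in gap detectable with 80% power is about 35 to 44 points. For a 22-point change the power is about 29% to 41%.

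**The case against.** The best defence is that Design & procedure states the intent to compare effectiveness between the two ethnic groups and sets recruitment targets for it. The covariate list is introduced as examples and does not rule out an interaction term, and such a term is the kind of detail that an article leaves to the full protocol or the analysis plan. This stands in part: the ethnic comparison was clearly in mind, and a missing interaction term would not by itself be a fault. But the Objectives are not silent. They state an operationalisation that does not match the question. An analysis plan faithful to that sentence would inherit the mismatch, and one that added an interaction would depart from it.

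A reader might infer more than the article supports:

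- *That the trial's main objective has no analysis.* Inequality is the secondary research question. The primary question, on knowledge and communication, has its own mixed-model analysis.
- *That randomisation is unstratified by ethnicity.* The article does not describe the randomisation method, and that silence is no finding.
- *That power for the interaction is 29%.* This is a general rule for an interaction as large as a main effect powered at 80%. It is not a figure for this trial, whose event rates are not given.
- *That the mixed models also need an ethnicity interaction.* The inequality question concerns the pursuit of LDKT, not the questionnaire scores.

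**Conclusion.** The concern holds as a stated mismatch between the secondary question and its operationalisation. The outcome definitions, the Cox contrast and the graphs follow the operationalisation; the ethnic comparison promised in Design & procedure is not carried into them. A positive pooled arm effect does not show that inequality fell.

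The size can only be illustrated. With 40 patients per cell and the assumed rates, a gap widening from 20 to 32 points goes with a significant pooled test in about 63% of trials, and an unchanged 20-point gap in about 87%. These percentages depend on the assumed rates and even split; the conclusion that the pooled contrast does not measure the gap does not. The proper contrast will be imprecise at this sample size. That limits what can be claimed and is no reason to substitute the pooled comparison.

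**What to change.** 1. Reword the operationalisation in Objectives and reconcile it with Design & procedure, Statistical analysis and Discussion, so that all four describe the same question.
2. Name one arm-by-ethnicity contrast and its scale. Preferably use the absolute scale: the between-arm difference in the Dutch minus non-Dutch gap in 12-month LDKT activity, estimated from the four arm-by-ethnicity risks with a confidence interval.
3. Report any Cox arm-by-ethnicity interaction separately and label it a relative measure, since it can disagree with the absolute gap.
4. Report arm effects and absolute risks within each ethnic group, with confidence intervals.
5. State that the trial was sized for the overall arm contrast, so the interaction will be imprecise, and that no conclusion about inequality will be drawn from the pooled comparison alone.

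The cost is one extra analysis on data already being collected, and a more modest conclusion. Recruitment and sample size need not change.
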